### Model training and evaluation

The primary model development will be based on a dataset of 512 patients. Within this cohort, we will implement stratified k-fold cross-validation (typically 5- or 10-fold, depending on the final class distribution) where possible to assess model robustness and mitigate overfitting. Image-based deep learning models require extensive computational resources, therefore, cross-validation will be applied more selectively. We will therefore use a fixed training/validation/test split for imaging data, ensuring non-overlapping patient groups. Early model experiments will be conducted using internal validation on the training data with hold-out validation to optimize architecture and hyperparameters. Final model evaluation will be performed on an independent hold-out test set.

This hold-out test set will be compiled prospectively during the course of the study after model development, using newly enrolled patients not included in the training dataset. This temporal separation will ensure unbiased performance evaluation of the final model.

Model performance will be evaluated on the independent hold-out test set using several complementary performance metrics. These will include the area under the receiver operating characteristic curve (AUROC), the area under the precision-recall curve (AUPRC), overall accuracy, sensitivity, specificity, F1-score, as well as positive and negative predictive values. Calibration will be assessed using appropriate measures, such as the Brier score, Hosmer-Lemeshaw-Test and calibration curves. Clinical decision-making utility can additionally be evaluated using decision curve analysis (DCA).

Importantly, our models are designed to output individualized risk probabilities, not dichotomous predictions. As such, the selection of a cut-off point for potential clinical decision-making will be a post-modelling step, and risk thresholds for high-risk patient classification will not be predefined. Instead, various thresholding strategies will be explored post hoc, including Youden’s index (for balanced sensitivity and specificity), cut-offs optimized for specific clinical priorities (e.g., maximizing sensitivity), and thresholds guided by DCA.

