### Three predictive models will be developed

First, a model based on deep learning using lung ultrasound images, second, a model based solely on clinical variables using common frameworks like automated machine learning (AutoML), and finally, a combined model integrating both clinical and imaging features.

The dataset will be split using stratified, patient-wise sampling into non-overlapping training and hold-out test sets. Internal model performance will be assessed using k-fold cross-validation within the training set, and final evaluation will be conducted on the independent test set. Full details of the modelling and validation procedures are provided in the statistical methods.

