**Fig 2 pone.0329076.g002:**
[figure not shown]
Graphic representation of the lung ultrasound areas. Lung ultrasound will be performed in 12 areas, 6 in each hemithorax. Areas are separated by the anterior and posterior axillary line into an anterior, lateral and posterior zone and a superior and inferior area.

The criteria for including imaging data are described above (“Eligibility Criteria”). If these conditions are not met, the interpretability of the ultrasound is considered insufficient.

To maximize inclusiveness and minimize selection bias, operators are encouraged to adjust technical parameters (e.g., depth and gain) during image acquisition in order to meet these quality criteria. A convex transducer was selected to allow visualization of deeper structures across a wide range of patient anatomies.

The performing physicians are experienced in perioperative medicine and critical care and will be trained in ultrasound methodology before the start of the study.

After transmission and storage in the PACS of the Department of Radiology, image pre-processing and artifact correction are performed before the data serves as input for the machine learning model. Images are not labeled by human experts; only the pre-defined endpoint POPC serves as labels for the imaging data.

The clinical data obtained for the study correspond to parameters routinely collected during anesthesiologic preoperative evaluation, the course of anaesthesia during surgery, and postoperatively in the recovery room. Plausibility checks are carried out on the numerical data; if these deviate from the valid value range, they are removed. Missing data may be imputed by different methods as described below.

Based on the collected data and the outcome parameters (description in chapter “Outcome”), machine learning algorithms will be trained to predict POPC by outputting an individual patient’s percentage risk of suffering a postoperative pulmonary complication.

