### Addressing overfitting and class imbalance

Overfitting will be addressed through the implementation of several regularization techniques commonly used in deep learning. These include dropout layers within the network architecture, L2 weight regularization to penalize large weights, and data augmentation techniques applied to ultrasound images (e.g., rotation, flipping, and zooming). Model complexity will also be restricted as needed.

To better estimate the prevalence and clinical relevance of POPC, we conducted a preliminary single-center observational study involving 259 patients undergoing surgery under general anesthesia. The cohort included 106 female patients (41%) and 62 current smokers (24%) with a median age of 66 years. Overall, 111 patients (43%) experienced at least one POPC, indicating that POPC is a relatively frequent complication in the targeted patient population [25].

Based on this preliminary observational data, only moderate class imbalance is to be expected. Nevertheless, additional strategies will be employed to ensure balanced learning. These include maintaining class ratios across cross-validation folds, monitoring class-wise performance metrics, and using class weighting techniques if imbalances are observed in specific subgroups.

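### The Hosmer-Lemeshow test is a weak calibration measure for models that output percentage risks; calibration intercept and slope with confidence intervals would be a cheap improvement (minor)

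*Protocol article*

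**What the plan says.** Under Model training and evaluation the article names three calibration measures as examples: "Calibration will be assessed using appropriate measures, such as the Brier score, Hosmer-Lemeshaw-Test and calibration curves". The setting is external to model fitting: "Model performance will be evaluated on the independent hold-out test set using several complementary performance metrics".

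The product is a probability. The same section says "our models are designed to output individualized risk probabilities, not dichotomous predictions", and Study measures describes "outputting an individual patient’s percentage risk of suffering a postoperative pulmonary complication". Decision curve analysis and exploratory risk thresholds are then built on these risks.

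The size of the evaluation set is not given, and the article describes the set in more than one way. The section on the three predictive models says "The dataset will be split using stratified, patient-wise sampling into non-overlapping training and hold-out test sets". Model training and evaluation says "The primary model development will be based on a dataset of 512 patients" and that the hold-out set is compiled "using newly enrolled patients not included in the training dataset". A paragraph under Adverse events and harms describes development on the whole dataset with cross-validation, plus a temporally independent validation set.

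No p-value rule, number of risk groups, degrees of freedom or calibration limit is stated. The analysis plan (S3 File) is not shown.

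**The concern.** The null hypothesis of the Hosmer-Lemeshow test is that predicted and observed risks agree. The test can therefore favour a model only by failing to reject, and that failure carries no bound on how wrong the risks may be. It is the only formal test among the three named measures.

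The Brier score does not fill the gap, because it mixes discrimination with calibration and moves little when all risks are shifted. The calibration curve does show size and direction, but it is descriptive.

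At stake is how far the reported percentage risks, and any thresholds and decision curves built on them, can be trusted. A systematic shift of several percentage points, mild overconfidence or underconfidence could pass the test in a small evaluation set.

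**Working it through.** **Plan's own figure.** There is none for calibration. The 512 patients were derived for comparing AUROC 0.83 with 0.93, so nothing has to be reproduced here.

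**Inputs from the article.** Prevalence 43% (111 of 259, Addressing overfitting and class imbalance); AUROC 0.83 for ARISCAT and 0.93 as the target (Sample size); 512 patients.

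**Assumptions.** Evaluation set of 0.20 × 512 = 102 or 0.30 × 512 = 154 patients; normally distributed linear predictor; 10 equal risk groups; alpha 0.05; reference of 10 df, because nothing is fitted on hold-out data.

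**Statistic.** H = Σ (O_g − E_g)² / [n_g p̄_g (1 − p̄_g)], summed over 10 groups, where O_g and E_g are observed and expected events and p̄_g is the mean predicted risk. H is compared with the 95% point of chi-square on 10 df (18.31).

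**Simulated detection rates** (4000 replicates), n = 102 / n = 154:

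| Miscalibration | AUROC 0.83 | AUROC 0.93 |
|---|---|---|
| All risks 0.5 logit too high | 0.23 / 0.33 | 0.18 / 0.24 |
| Slope 0.8 (mild overfitting) | 0.23 / 0.28 | 0.32 / 0.36 |
| Slope 0.7 | 0.47 / 0.54 | 0.49 / 0.59 |
| Slope 0.6 | 0.74 / 0.85 | 0.69 / 0.83 |
| Slope 0.5 | 0.92 / 0.98 | 0.88 / 0.96 |
| Slope 1.3 (underconfident) | 0.02 / 0.04 | 0.01 / 0.01 |

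One minus these rates gives the misses: 67 to 82% for the shift (66 to 83% over repeated runs), 64 to 77% for slope 0.8, 41 to 53% for slope 0.7, 15 to 31% for slope 0.6, and 96 to 99% for slope 1.3. At n = 512 and AUROC 0.83, power is 0.91 for the shift, 0.91 for slope 0.7 and 0.48 for slope 0.8.

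**Analytic check of the shift.** A logit shift δ moves each risk by about δ·p(1 − p), so the noncentrality is λ ≈ δ²·n·E[p(1 − p)]. For a calibrated model, E[p(1 − p)] equals the Brier score: 0.161 at AUROC 0.84 and 0.102 at 0.93.

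- The mean risk is too high by about 0.5 × 0.161 = 0.08 at AUROC 0.84, and by 0.5 × 0.102 = 0.05 at 0.93.
- AUROC 0.84: λ = 0.25 × 102 × 0.161 = 4.1, and 6.2 at n = 154. On 10 df this gives power 0.22 / 0.33. The same λ on 1 df gives 0.53 / 0.70.
- AUROC 0.93: λ = 2.6 / 3.9. On 10 df the power is 0.15 / 0.21; on 1 df it is 0.36 / 0.51.
- AUROC 0.84, n = 512: λ = 20.6, power 0.90 on 10 df.

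These agree with the simulation to within a few points. They also show why the test is weak here: a one-parameter departure is spread over 10 df.

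**Comparison with the alternative** (1500 replicates), n = 102 / n = 154:

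- Shift 0.5, AUROC 0.83: calibration-in-the-large detects 0.55 / 0.73, against 0.24 / 0.34 for Hosmer-Lemeshow.
- Shift 0.5, AUROC 0.93: 0.39 / 0.54 against 0.19 / 0.23.
- Slope 0.7, AUROC 0.83: the slope CI excludes 1 in 0.48 / 0.64, against 0.47 / 0.55. Its median width is 0.59 / 0.48.
- Slope 0.7, AUROC 0.93: 0.47 / 0.60 against 0.49 / 0.59.

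**Brier score under the shift.** It moves from 0.161 to 0.169 (AUROC 0.84) and from 0.102 to 0.107 (AUROC 0.93).

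**Degrees of freedom.** The familiar g − 2 = 8 df belongs to the data on which a logistic model was fitted. If it were used on hold-out data, a calibrated model would be rejected with probability P(χ²₁₀ > 15.51) = 0.115 in theory, and in about 12 to 15% of simulated samples, instead of 5%.

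**The case against.** The list is introduced as examples, so it is open, and it includes calibration curves, which show the size and direction that the test lacks. Degrees of freedom, grouping and any calibration limits are ordinary content of an analysis plan that is not shown. The sized claim is about AUROC, thresholds are exploratory and chosen after modelling, and evaluation is offline. All of this stands, and it is why the point is minor.

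Four stronger readings are tempting, and the documents do not support them.

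- A reader might infer that p above 0.05 will be taken as proof of calibration. No such rule is written.
- A reader might infer that the test generally misses relevant miscalibration more often than not. That holds for shifts, mild overfitting and underconfidence at the assumed sizes. It does not hold for slope 0.6 or worse, or for slope 0.7 with 512 test patients. The evaluation set may be newly enrolled patients in unstated number rather than a fraction of 512.
- A reader might say that the test misleads in both directions. The miss rates belong to the 10-df version and the 12 to 15% false rejection to the 8-df version; they cannot be charged to one test, and the article names neither.
- A reader might infer that the plan makes miscalibration likely. Class weighting is conditional ("using class weighting techniques if imbalances are observed in specific subgroups"), only moderate imbalance is expected, and dropout, L2 penalties, augmentation and limits on complexity are planned against overfitting.

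The alternative is also no cure for a small test set: for slope 0.7 at n = 102 it detects no more than Hosmer-Lemeshow.

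**Conclusion.** The concern holds as a minor point. The article names a test that gives neither size, direction nor uncertainty of miscalibration, for models whose output is a percentage risk. A non-significant result from it would be weak evidence of calibration. With an assumed 102 to 154 evaluation patients and 43% prevalence, it would overlook most 0.5-logit shifts, most mild overfitting and nearly all underconfidence of slope 1.3. Slope 0.7 is close to even odds, and marked overfitting is usually found. These figures depend on the assumed evaluation size and on a normal linear predictor, and the shift and slope 0.7 are found about 91% of the time at n = 512 (AUROC 0.83). The planned calibration curves partly cover the gap. What remains is that a better and nearly free measure is available.

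**What to change.** In Model training and evaluation, replace the Hosmer-Lemeshow test, or make it secondary, with two estimates on the evaluation set for all three models, each with a 95% CI:

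- calibration-in-the-large, the intercept of a logistic fit with the model's logit as offset;
- the calibration slope.

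Report them next to the calibration curve with a confidence band, and state that a non-significant test will not be reported as evidence of calibration. Limits for calling a model calibrated, fixed before the evaluation set is opened, are optional.

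The gain is about twice the detection of a systematic shift, together with direction and visible uncertainty. The cost is one amended sentence and two logistic fits per model, with no new data. The downside is that with a small evaluation set the intervals will be wide (about 0.6 for the slope at n = 102 when the true slope is 0.7), so calibration may have to be reported as inconclusive.

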### Addressing overfitting and class imbalance

Overfitting will be addressed through the implementation of several regularization techniques commonly used in deep learning. These include dropout layers within the network architecture, L2 weight regularization to penalize large weights, and data augmentation techniques applied to ultrasound images (e.g., rotation, flipping, and zooming). Model complexity will also be restricted as needed.

To better estimate the prevalence and clinical relevance of POPC, we conducted a preliminary single-center observational study involving 259 patients undergoing surgery under general anesthesia. The cohort included 106 female patients (41%) and 62 current smokers (24%) with a median age of 66 years. Overall, 111 patients (43%) experienced at least one POPC, indicating that POPC is a relatively frequent complication in the targeted patient population [25].

Based on this preliminary observational data, only moderate class imbalance is to be expected. Nevertheless, additional strategies will be employed to ensure balanced learning. These include maintaining class ratios across cross-validation folds, monitoring class-wise performance metrics, and using class weighting techniques if imbalances are observed in specific subgroups.

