### Sample size

Predicting POPC for the clinician is difficult on a case-by-case basis. Therefore, several scoring systems have been developed in the past. The most common of these, the ARISCAT score, has an AUROC of 0.83 [15]. It should be noted that the current literature does not provide any further metrics such as area under the precision-recall curve (AUPRC) or F1 score on the ARISCAT [15,16]. We therefore used the AUROC as the reference metric. The model we aim to create should be significantly better than the ARISCAT score and thus have at least an AUROC of 0.93. Achieving this seems realistic since, in the preliminary work of our research group, prediction models for various postoperative complications have already been created, whose predictive accuracy is in this range [17,18]. With a significance level of 0.05 and a power of 80%, 512 patients would be needed to create the database based on the method described by Hanley and McNeil for comparing ROC curves [19].

Patients are stratified according to the risk criteria determined by ARISCAT so that approximately equal numbers of patients are included in each of the low-risk (ARISCAT < 26 points), intermediate-risk (ARISCAT 26–44 points), and high-risk (ARISCAT ≥ 45 points) groups.

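### Class weighting triggered by subgroup imbalance conflicts with a model meant to output individual risks; the damage is mild for one overall weight and large for weights set within subgroups

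*Protocol article*

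**What the plan says.** On the product, the article is clear. Under Study measures, the algorithms predict POPC by "outputting an individual patient’s percentage risk of suffering a postoperative pulmonary complication". Under Model training and evaluation, "our models are designed to output individualized risk probabilities, not dichotomous predictions". That section leaves cut-offs to a later step and lists three routes: Youden's index, cut-offs serving a clinical priority such as sensitivity, and decision curve analysis. It places the performance evaluation on the hold-out test set and names the Brier score, the Hosmer-Lemeshow test and calibration curves for calibration.

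On class balance, the section Addressing overfitting and class imbalance reports from a preliminary cohort of 259 that "Overall, 111 patients (43%) experienced at least one POPC" and concludes that "only moderate class imbalance is to be expected". It still plans extra measures, one of which is "using class weighting techniques if imbalances are observed in specific subgroups". The subgroups, the degree of imbalance that triggers weighting and the weight formula are not given.

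On case mix, the Sample size section stratifies recruitment so that "approximately equal numbers of patients are included in each of the low-risk", intermediate-risk and high-risk ARISCAT groups. The section on recruitment describes pausing a group once it is ahead of the others.

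**The concern.** A class weight changes the event rate that the model believes it is fitting. For a classifier judged only on ranking, an overall weight does little harm. For a model whose product is a percentage risk, the output stops being a risk unless it is corrected. Net benefit in decision curve analysis, the Brier score and the calibration curve all read the output as a probability.

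The trigger adds to the problem. Event rates should differ between ARISCAT groups; the Sample size section credits the score with an AUROC of 0.83, which would be impossible if they did not. A low event rate among low-risk patients is information that the model should learn. If weights are set within such groups, low-risk patients are pushed up and high-risk patients down. The model then gives away separation that ARISCAT keeps, although the main hypothesis is that it outperforms such scores.

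Timing matters too. If miscalibration first shows on the hold-out test set, correcting it there would use the test data for development.

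**Working it through.** **The plan's own figure.** 111/259 = 0.4286, which rounds to the stated 43%.

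**Formula.** Balanced weights bring a group with event rate q to 50/50. They multiply the fitted odds by w = (1 − q)/q. A true risk p is then output as w·p / (1 − p + w·p).

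**One overall weight at the expected rate.** w = (259 − 111)/111 = 148/111 = 1.33.
- p = 10%: 1.333 × 0.10 / (0.90 + 0.133) = 12.9%
- p = 20%: 1.333 × 0.20 / (0.80 + 0.267) = 25.0%
- p = 43%: 50%

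The multiplier is the same for everyone, so the ranking does not change.

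**Weights set within a subgroup (event rates assumed; the article gives none by subgroup).**

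| Subgroup event rate | Odds multiplier | Output for true 10% | Output for true 20% |
|---|---|---|---|
| 20% | 0.80/0.20 = 4 | 31% | 50% |
| 10% | 0.90/0.10 = 9 | 50% | 69% |

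Above 50% events the shift is downward. At 70%, w = 0.30/0.70 = 0.43, and a true 70% is output as 50%.

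**Simulation with fitted models.** Logistic model, three equal risk groups, 512 patients for training, 50,000 for testing, 100 repeats. Group rates of 15/44/70% and the predictor strength are assumptions.

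| Weighting | Mean prediction, low/intermediate/high | AUROC | Brier |
|---|---|---|---|
| Observed rates | 14.7 / 43.8 / 69.9% | – | – |
| None | 14.7 / 44.4 / 69.7% | 0.874 | 0.143 |
| One overall weight | 17.7 / 49.4 / 73.9% | 0.874 | 0.145 |
| Within subgroup | 38.4 / 48.6 / 55.7% | 0.816 | 0.175 |

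**Sensitivity to the assumed rates, within-subgroup weighting.**
- Rates of 25/43/61%: the mean prediction in the low-risk group is 42%; AUROC goes from 0.839 to 0.815 and Brier from 0.162 to 0.176.
- Rates of 10/44/75%: the mean prediction in the low-risk group is 37%; AUROC goes from 0.896 to 0.819 and Brier from 0.130 to 0.174.

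**The severe end.** Rates of 15/40/74% (mean 43%), a within-stratum slope of 1, and the full shift log((1 − q)/q) added in each stratum. AUROC falls from about 0.84 to 0.74 and Brier rises from about 0.16 to about 0.21. In the same scenario, one overall weight leaves AUROC at 0.844 and takes Brier from 0.159 to 0.161. If the model sees a single score that carries all the risk, within-stratum weights leave AUROC at 0.844, but Brier still rises to 0.184.

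**The case against.** The strongest reply is that the harmful version is only one reading. Subgroup imbalance is the condition for weighting. The article does not say that weights are then computed within subgroups, that each subgroup is brought to 50/50, or that the subgroups are the ARISCAT groups. Ordinary overall weights may be meant, and at 43% events their effect is small. This stands, and it is why the size must be given as a range.

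Other points on this side also stand:
- A reader might infer that no recalibration is planned. The documents do not support that: the article refers to an SAP in S3 File, which is not shown and could contain such a step. Only the article's silence can be stated.
- A reader might take weighting as certain. Differing event rates are very likely, but no trigger level is defined.
- Decision curve analysis is optional and one of three routes to a threshold. Youden and sensitivity-based cut-offs need only ranking, which an overall weight leaves intact.
- A reader might infer that study patients would be overtreated. Under Study setting, the data are evaluated offline, without interaction between staff and the algorithm. The harm is to the model and its reported performance.

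Planned calibration checks do not answer the point. The article places them on the hold-out test set and names neither an action if they fail nor a check by ARISCAT group. An overall curve can also hide upward and downward errors in different groups.

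**Conclusion.** The point holds as a conflict between a stated method and the stated product. If class weighting is applied, the outputs are not the individual risks that the article promises, and its own 43% event rate gives little reason to apply it.

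With one overall balanced weight the cost is small: a shift of about 7 percentage points at a risk of 43%, no loss of AUROC, and about 0.002 on the Brier score. With weights set within subgroups it is large: across the assumed rates, fitted models put the mean prediction in the low-risk group at 37% to 42% where the true rate was 10% to 25%. AUROC fell by 0.024 to 0.077 (0.839 − 0.815; 0.896 − 0.819).

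A drop in AUROC of about 0.10 is tempting as a headline. It needs full balancing in every stratum and the assumed 15/40/74% rates, and it vanishes if one score carries all the risk, so it is not a prediction for this study. All subgroup figures rest on assumed event rates.

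**What to change.** In Addressing overfitting and class imbalance, remove the subgroup-triggered class weighting for the models that output probabilities, and say that differences in event rate between subgroups are left for the model to learn.

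If weights are kept for training stability:
- use a single overall weight, not subgroup-specific ones. An intercept update or logistic recalibration with a positive slope keeps the ranking, so it cannot restore ranking lost to subgroup weights;
- recalibrate by intercept update or logistic recalibration on out-of-fold predictions, or on validation-set predictions for the imaging model with its fixed split, before the test set is opened;
- report calibration by ARISCAT group as well as overall.

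If the SAP already provides for this, one sentence of cross-reference in the article is enough. The cost is a sentence of text and slightly more analysis work. Without weights, sensitivity at a default cut-off of 0.5 may be lower, but the plan does not use that cut-off.
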